### Intervention

Screen-positive women fulfilling the criteria will be enrolled after written informed consent.

### Randomization, allocation, and blinding

Women enrolled will be randomized using a randomization chart which will be generated with the help of computer-generated random numbers. Participants will be randomized in a ratio of 1:1 to either receive 75 mg or 150 mg aspirin at night from 12 to 16 weeks of pregnancy. Low-dose aspirin will be administered at night with a full stomach, as it had been found to be significantly more effective in reducing the risk of pre-eclampsia and fetal growth restriction than when administered in the morning.

Trial drugs will be packed according to the randomization chart and will be delivered at the trial site. The randomization schedule will be strictly controlled, and the blinding of the trial drugs will be done by following the method of sequential number order. The medicine box will be serially numbered according to the participant’s enrolment number and will be dispensed accordingly. Participants, researchers, and managing clinicians will be blinded to the treatment. The trial will be two-armed prospective double-blind randomized control trial carried out over a period of 36 months. Unblinding during the trial will only be undertaken in the event of any serious adverse event (SAE).

To ensure the integrity of blinding in this trial, the preparation and packaging of the trial drugs will be managed by a pharmaceutical company. Here is how the process will be handled:

*Independent blinding and packaging*

To ensure the integrity of double blinding and maintain confidentiality, we will contract a reputable pharmaceutical company to handle the blinding process. In India, we have access to 75 mg and 150 mg dosages of aspirin tablets. The pharmaceutical company will manage the preparation and packaging of these dosages:

Low-dose aspirin (75 mg): this will be provided as one 75 mg tablet in an empty gelatin capsule.

Low-dose aspirin (150 mg): this will be provided as two 75 mg tablets in an empty gelatin capsule.

Due to the larger size of the 150 mg aspirin tablet, it is not feasible to put a single tablet in a similar capsule for blinding purposes. Therefore, two 75 mg aspirin tablets will be used to represent the 150 mg dose, ensuring that both dosage forms are indistinguishable in appearance, taste, and packaging for blinding purposes.

Strict protocols will be followed to maintain the confidentiality of the medication and prevent any identifying features that could reveal the treatment allocation.

*Randomization and control*

An independent statistician, who has no role in the drug preparation or handling, will overlook the randomization process. This statistician will create the computer-generated randomization sequence to ensure that treatment assignments are concealed. The pharmaceutical company will use this sequence to label the medications.

*Labeling and distribution*

Labels will be designed to mask the treatment assignment from both participants and study staff, with uniform packaging that does not disclose any treatment information.

*Monitoring and compliance*

Regular audits and checks will be performed to ensure compliance with blinding procedures and to quickly address any potential breaches. Any issues with blinding will be documented and resolved promptly.

*Allocation sequence generation*

In our trial, the allocation sequence will be generated by an independent statistician using a validated computer program. This will ensure that the process is fully randomized and minimizes potential bias. The software used guarantees that the sequence is random and secure, preventing any influence from external factors or manipulations.

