##### Blinding of allocation

The allocation sequence will be concealed using secure methods, such as sealed envelopes or electronic randomization systems. Access to the sequence will be restricted to authorized personnel, and it will be revealed only after enrollment and completion of the study.

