#### Adherence support

◦ Medication reminders: automated reminders, including text messages and phone calls, will be employed to assist participants in remembering to take their medication as prescribed.◦ Adherence aids: participants will be provided with a bottle containing their medication for a specific number of weeks as per protocol. At each subsequent visit, the research team will check the remaining tablets to assess adherence, ensuring that participants have taken the prescribed medication as per the protocol. This method allows for regular monitoring of compliance and helps to ensure accurate tracking of medication intake throughout the trial.

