#### Procurement of trial drugs

Both the aspirin dosages will be available in granules form in identical capsules. Both trial drugs will be packed only for research purposes by the GMP-certified company.

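### The blinded product is described in two incompatible ways, and any SAE is enough to break the code, whether or not care depends on knowing the dose

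*Protocol article*

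**What the plan says.** The protocol article describes the trial drug in two places.

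- Randomization, allocation, and blinding. For 75 mg: "this will be provided as one 75 mg tablet in an empty gelatin capsule". For 150 mg: "this will be provided as two 75 mg tablets in an empty gelatin capsule". The section gives the result as "ensuring that both dosage forms are indistinguishable in appearance, taste, and packaging for blinding purposes".
- Procurement of trial drugs: "Both the aspirin dosages will be available in granules form in identical capsules".

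On who is blinded, the first of these sections states: "Participants, researchers, and managing clinicians will be blinded to the treatment". On handling, Adherence support states: "At each subsequent visit, the research team will check the remaining tablets to assess adherence". Regular monitoring and follow-up asks for unused medication back at each visit.

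On opening the code there are also two statements.

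- Randomization, allocation, and blinding: "Unblinding during the trial will only be undertaken in the event of any serious adverse event (SAE".
- Blinding of allocation, speaking of the sequence: "it will be revealed only after enrollment and completion of the study".

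**The concern.** Double blinding is central to this trial: it is in the title and is part of the novelty the authors claim. The hypothesis is directional (150 mg better than 75 mg). Several outcomes leave room for judgement, among them symptom-based criteria for pre-eclampsia, mode of delivery, and admission to NICU or HDU/ICU. If staff or participants can tell the capsules apart, or if codes are opened more freely than care requires, these assessments lose some of their protection.

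Two things look wrong. First, a reader cannot tell which product was blinded, and one of the two descriptions does not support the assurance attached to it. Second, the code-break rule is triggered by the seriousness of an event, not by whether knowing the dose would change what is done for the woman or newborn.

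**Working it through.** No figure in the plan is in dispute, so the check is mainly a comparison of sections.

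**1. The product.**

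| | Randomization, allocation, and blinding | Procurement of trial drugs |
|---|---|---|
| 75 mg | one tablet in a capsule | granules in a capsule |
| 150 mg | two of the same tablets in a capsule | granules in a capsule |
| Basis for the match | appearance, taste, packaging | capsules said to be identical |

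No other section reconciles these. Method of administration speaks of one capsule at bedtime, which fits either. Adherence support speaks of remaining tablets, which settles nothing.

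**2. What could differ if tablets are used as written.** The contents are in the ratio 2 × 75 mg : 1 × 75 mg = 2:1 by tablet count. No filler or dummy tablet is mentioned. Weight, sound on shaking and content on opening could then differ, and the assurance names none of the three. Granules could be made up to match, which is why it matters which description is true.

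**3. Who could notice.** Treatment period gives 21–25 weeks, so a woman handles about 21 × 7 = 147 to 25 × 7 = 175 capsules, all from one arm. Staff handle both arms. Visits 2–12 combine dispensing, blood pressure and symptom history. Study procedure at follow-up has the home-visiting officer cover drug supply, compliance and general follow-up. The Blinding paragraph under Assignment to interventions separates only those who assign treatment from those who collect data or assess outcomes.

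**4. The code-break rule.** Any SAE is sufficient. Eclampsia, HELLP, abruption and ICU stay are listed secondary outcomes and plausible SAEs, so code-breaks can follow outcome and, if the doses differ in effect, arm. The statement that the sequence stays closed until completion does not mention this exception.

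**5. Can a code-break alter the primary outcome?** The primary outcome is onset of preterm pre-eclampsia before 37 weeks. If pre-eclampsia is itself the SAE, the event has occurred before the code is opened. Stillbirth, delivery or NICU admission come at or after the end of the pregnancy. That woman's primary status is then already fixed. What remains open is her later secondary and safety data, and the chance that staff who learn one allocation link it to a capsule cue. An SAE unrelated to pre-eclampsia in a woman still under observation would be an exception, but the document gives no rate for these.

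**6. Scale, for orientation only.** The plan's 147 per group reproduces from its inputs (17% v 6.5%, two-sided 5%, 80% power). 294/0.8 = 367.5, close to the stated 370. Expected primary events:

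- 185 per group: 185 × 0.17 = 31.5 and 185 × 0.065 = 12.0, total 43.5.
- 147 per group: 25.0 and 9.6, total 34.5.

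The share of these that would be SAEs is not given. Assuming 25%, 50% or 100% of the 43.5, about 11, 22 or 43 women would be eligible for unblinding through the primary outcome. These are counts of eligibility under an assumption. They do not count codes broken, and they leave out SAEs other than primary events.

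**The case against.** **The blind is protected elsewhere.** An outside company packs the drug, an independent statistician holds the sequence, labels and packaging are uniform, audits of blinding are planned, and the article promises to avoid features that reveal allocation. Capsule size, tablet size and filler are manufacturing details that a condensed article may leave to the full protocol. This stands in part. The absence of a filler from the article is not itself an error, and a difference in weight or rattle is an inference that holds only if the tablet description is the product packed. It does not explain two incompatible descriptions of that product.

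**Staff may not see the contents.** Assessment of drug compliance and Drug compliance ask only for the empty container. That is fair, but Adherence support and Regular monitoring and follow-up have remaining drug checked and returned, so exposure is at least allowed for.

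**The primary outcome is fairly objective.** It rests on fixed blood pressure thresholds, usually on two occasions, with an automated dipstick reader and quantified protein. Headache and visual symptoms count only without proteinuria. This stands and limits the harm.

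**The SAE rule is a restriction, not an instruction.** It says when unblinding may happen, not that every SAE leads to it, and SAEs are not defined in the article. This stands. A reader might infer that the rule would unblind most women who reach the primary endpoint and so bias it. The document does not support that: the share of events that are SAEs is not given, and a code opened after onset cannot change whether the event is counted.

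**Releasing the sequence differs from opening one code.** The two statements can be read that way, but the article does not say so.

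**Conclusion.** The contradiction about the product is firm and rests on the text alone: tablets in one section, granules in another. The possible mismatch of capsules is conditional on the tablet description being what was packed without added matching material. In that case it applies to every capsule in the trial, with contents at 2:1, and the assurance given does not cover the properties most likely to differ.

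The code-break rule is badly fixed because it lacks any test of need and is not aligned with the statement on when the sequence is revealed. Its likely effect is on later secondary and safety outcomes and on staff learning capsule cues, not on whether that woman's primary event is counted. The number of women affected cannot be derived from the document.

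A reader might conclude that the double blind has failed or is unsecured. The article does not show that. It shows that the description does not establish the blind, and that a cheap correction would. The change should be made; the sample size is unaffected.

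**What to change.** 1. Reconcile Randomization, allocation, and blinding with Procurement of trial drugs so that one formulation is stated, namely the one actually packed.
2. If tablets are over-encapsulated, match the contents with an inert filler or dummy tablet, confirm that the two capsules agree in weight and sound, and state that this was done.
3. Limit code-breaking to cases where knowing the allocation is needed for the care of the woman or newborn. Log each break with date, reason and who was told, and keep outcome assessors blind afterwards.
4. Align the unblinding sentence with Blinding of allocation, separating the opening of a single code from the release of the whole sequence.

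The cost is protocol wording and, if tablets are used, a small packing cost for later batches. Screening and recruitment began on 1 May 2024, so if unmatched capsules have already been dispensed, those women cannot be re-blinded. The report should then say which batches were affected.

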### Allocation sequence and participant enrollment procedures

#### Generation of allocation sequence

##### Responsibility

The allocation sequence will be generated by an independent statistician who is not involved in participant recruitment or intervention assignment. This approach will ensure the integrity and randomness of the allocation process.

##### Method

The sequence will be created using a computer-generated random number sequence or specialized randomization software designed for clinical trials. The allocation sequence will be kept confidential to prevent any potential bias.

#### Enrollment of participants

Participants are enrolled by our research team, including principal investigators and research coordinators/scientist. This team will be responsible for screening and enrolling participants according to the study criteria.

##### Principal investigator (PI)

PI will oversee the entire enrollment process, ensuring that the study protocols and eligibility criteria are strictly followed. PI will be responsible for the final approval of participant eligibility and informed consent.

##### Research coordinators/scientist

Research coordinators/scientist will manage the day-to-day enrollment activities, including screening potential participants, obtaining informed consent, and collecting baseline data.

##### Healthcare professionals

In some cases, healthcare professionals such as residents/physicians or nurses may assist in identifying potential participants and providing initial study information. However, the final decision on enrollment and intervention assignment will be managed by the research team.

#### Incidental support for trial participants

Incidental support for trial participants will cover travel costs and provide compensation for lost wages, ensuring they can attend study visits without financial hardship or impact on their livelihood. These measures will promote fairness and encourage full participation in the study.

#### Assignment to interventions

##### Process

Eligible participants who will provide consent will be assigned to interventions according to the pre-generated allocation sequence managed by the independent statistician.

##### Blinding

To maintain blinding, the assignment of participants to interventions will be conducted by personnel who are not involved in data collection or outcome assessment. This ensures that neither the participants nor the research staff are aware of the treatment assignments.

##### Blinding of allocation

The allocation sequence will be concealed using secure methods, such as sealed envelopes or electronic randomization systems. Access to the sequence will be restricted to authorized personnel, and it will be revealed only after enrollment and completion of the study.

#### Documentation and quality control

##### Documentation

All procedures related to the allocation sequence generation, participant enrollment, and intervention assignment will be meticulously documented. This will include records of the allocation sequence, enrollment logs, and intervention assignment details.

##### Quality control

Regular audits and reviews will be performed to ensure adherence to the study protocol and ethical standards. Any issues or discrepancies identified will be addressed promptly to maintain study integrity.

##### Study interventions (investigational products)

Group A: will receive 75 mg of aspirin at night with water starting 12–16 weeks till completed 37 weeks or earlier if onset of preterm PE.

Group B: will receive150 mg of aspirin at night with water starting 12–16 weeks till completed 37 weeks or earlier if onset of preterm PE.

#### Method of administration of investigational products

Every patient will be instructed to take one capsule at bed time starting from the time of enrolment. Aspirin will be stopped in both groups if a woman develops preterm PE, otherwise will be continued until completed at 37 weeks.

#### Counseling

All the participants will be counseled to take a capsule at night after dinner.

### Strategies to improve adherence to intervention protocols and monitoring procedures

#### Patient education and engagement

◦ **Detailed counseling:** Participants will receive comprehensive counseling on the significance of adhering to the study protocol, including the benefits of the intervention and the importance of consistent participation.◦ **Written instructions:** Participants will be provided with detailed written instructions covering dosage, timing, and method of administration of the trial drugs. These instructions will supplement verbal guidance.

#### Adherence support

◦ Medication reminders: automated reminders, including text messages and phone calls, will be employed to assist participants in remembering to take their medication as prescribed.◦ Adherence aids: participants will be provided with a bottle containing their medication for a specific number of weeks as per protocol. At each subsequent visit, the research team will check the remaining tablets to assess adherence, ensuring that participants have taken the prescribed medication as per the protocol. This method allows for regular monitoring of compliance and helps to ensure accurate tracking of medication intake throughout the trial.

### Regular monitoring and follow-up

◦ Scheduled visits: participants will attend regular follow-up visits to evaluate adherence and address any issues. During these visits, adherence will be assessed through communication and review of medication logs.◦ Tablet return: participants will be asked to return unused medication at each visit. This will help researchers track missed doses and assess adherence rates.◦ Laboratory tests: periodic laboratory tests will be conducted to monitor physiological changes or side effects related to the intervention.

### Addressing non-adherence

◦ Problem-solving: participants showing signs of non-adherence will be contacted to identify and address barriers they may be facing. Support strategies will be personalized, such as adjusting reminder schedules or offering additional help.

### Documentation and reporting

◦ Data analysis: adherence data will be systematically analyzed to identify trends and areas for improvement. This analysis will guide ongoing support strategies and necessary adjustments to the intervention protocol.

### Comparison

Primary objective will be to compare 75 mg versus 150 mg aspirin for the prevention of preterm preeclampsia in screen-positive high-risk women. Secondary objectives will be to evaluate fetomaternal outcomes in high-risk women receiving 75 mg versus 150 mg aspirin for the prevention of preterm preeclampsia. Participants will be followed and onset of preterm PE < 37 weeks will be recorded. In case the women develop preterm PE, the aspirin will be stopped. All participants developing PE and not developing PE women will be followed till delivery and fetomaternal outcome will be noted.

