### Need for the study

This study aims to address these gaps by comparing the effectiveness of 75 mg and 150 mg daily aspirin in preventing pre-eclampsia among high-risk pregnant women. By refining dosage guidelines, this research will help tailor preventive strategies more effectively and potentially improve maternal and fetal outcomes. Additionally, it will provide valuable insights into the long-term effects of aspirin on infant health, contributing to a more comprehensive understanding of its benefits and risks.

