**Intrapartum**
Bleeding—GI bleedGestational HTEclampsiaHELLPAbruptionAcute kidney injuryMode of delivery
*Postpartum*
Post partum hemorrhageHDU/ICU stayHematoma formationMortality

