#### Study procedure

All screen-positive women fulfilling the criteria will be enrolled at 12–16 weeks of pregnancy after signing the consent form. The required baseline investigations will be carried out and that day will be visit 1 or baseline. Previous obstetric history, pre-pregnancy weight, and past history of preeclampsia will be recorded. Weight and height will be recorded. Blood pressure will be measured on the right arm in a sitting position, and urine albumin/sugar test will be performed. After enrolment, the women will be randomized to receive 75 mg or 150 mg aspirin at night from 12 to 16 weeks of pregnancy. The drug will be dispensed to her after fulfilling all the formalities as per the protocol.

The subsequent follow-up will be at 20 weeks (visit 2), and four-weekly till 28 weeks, i.e., at 24 weeks (visit 3) and at 28 weeks (visit 4). After 28-week period of gestation, participants will be called two-weekly till 36 weeks, i.e., 30 weeks (visit 5), 32 weeks (visit 6), 34 weeks (visit7), and 36 weeks (visit 8). Participant will be called weekly after 36 weeks, i.e., 37 weeks (visit 9). Aspirin will be stopped at 37 weeks or earlier to 37 weeks if onset of preterm preeclampsia. If they do not develop PE, then they will be called weekly at 38 weeks (visit 10), 39 weeks (visit 11), and 40 weeks (visit 12). Subjects will visit the investigating site 12 times during the trial or if participant is not able to visit; a senior research fellow recruited in the project will visit her at her residence..Participants will be followed and whether they have onset of preterm PE < 37 weeks will be recorded. In case the women develop PE, the aspirin will be stopped. All participants developing PE and not developing PE women will be followed till delivery and fetomaternal outcome will be noted.

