#### Treatment period

It will be 21–25 weeks in both groups. Study participant will be recruited at 12–16 weeks. The subsequent follow-up will be at 20 weeks (visit 2) and four-weekly till 28 weeks, i.e., at 24 weeks (visit 3) and at 28 weeks (visit 4). After 28-week period of gestation, the participants will be called biweekly till 36 weeks, i.e., 30 weeks (visit 5), 32 weeks (visit 6), 34 weeks (visit7), and 36 weeks (visit 8). Participants will be called weekly after 36 weeks, i.e., 37 weeks (visit 9), 38 weeks (visit 10), 39 weeks (visit 11), and 40 weeks (visit 12). Onset of preterm PE will be recorded, aspirin will be stopped, and participants will be followed till delivery and fetomaternal outcome will be noted. In participants who do not develop preterm PE, aspirin therapy will be stopped at 37 completed weeks and will be allowed to go till 40 weeks (term) if no obstetrical indication for induction and fetomaternal outcome will be recorded. At every visit, history will be taken and they will be asked for any signs and symptoms of preeclampsia; weight and BP will be measured and urine albumin test will be done Fig. 1.

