#### Successive visits

The subsequent follow-up will be for 24–28 weeks. After enrolment (visit 1), participants will be followed up at 20 weeks (visit 2) and 4 weekly till 28 weeks, i.e., at 24 weeks (visit 3) and at 28 weeks (visit 4). After 28 weeks period of gestation, the patient will be called two-weekly till 36 weeks, i.e., 30 weeks (visit 5), 32 weeks (visit 6), 34 weeks (visit 7), 36 weeks (visit 8). Participant will be called weekly after 36 weeks, i.e., 37 weeks (visit 9), 38 weeks (visit 10), 39 weeks (visit 11), and 40 weeks (visit 12).

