#### Safety recording

Safety evaluation will be performed by recording clinical adverse events at randomization (baseline) and at the subsequent clinical visits. Further adverse events will be classified according to their type, severity, and possible relationship to treatment. At visit 1, the subject’s medical history will be recorded. At all visits, the vital signs, i.e., body temperature, pulse, blood pressure, will be recorded and urine for routine microscopy will be performed. Antenatal checkup will be performed as per hospital protocol and time and mode of delivery will also be as per obstetrical indication.

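### Follow-up is stated only to delivery, while listed neonatal and postpartum outcomes can occur after discharge; one short postnatal contact would close the gap

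*Protocol article*

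**What the plan says.** The Comparison section sets the end of follow-up for every woman: those who develop pre-eclampsia and those who do not "will be followed till delivery and fetomaternal outcome will be noted". Study procedure repeats the rule, and Treatment period has it again for women who develop preterm pre-eclampsia: "participants will be followed till delivery and fetomaternal outcome will be noted".

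The contact schedule is fixed. Study procedure says "Subjects will visit the investigating site 12 times during the trial", with a home visit if a woman cannot come. The list under Successive visits ends with "39 weeks (visit 11), and 40 weeks (visit 12", both in weeks of gestation.

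The fetal list under Secondary outcomes includes NICU admission, early neonatal death and intracranial bleeding. The maternal list has a postpartum block, printed without separators as "Post partum hemorrhageHDU/ICU stayHematoma formationMortality". No time window is attached to any of these.

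On harms, Safety recording says "Safety evaluation will be performed by recording clinical adverse events at randomization (baseline) and at the subsequent clinical visits". The Need for the study section says of the trial that "it will provide valuable insights into the long-term effects of aspirin on infant health".

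**The concern.** The stated end of observation comes before the time at which some listed outcomes can occur. A newborn death some days after birth, or a haematoma found after the mother has gone home, lies outside a follow-up that ends at delivery.

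These outcomes carry much of the safety question. The Introduction says that the safety of the 150 mg dose still needs validation, and it names postpartum haemorrhage, postpartum haematoma and neonatal intracranial haemorrhage among the harms reported in aspirin users. If such events are found only when they happen to fall within the birth admission at this hospital, the safety comparison rests on uneven observation time, and low counts in both groups could be read as reassurance. The sentence on long-term infant health raises an expectation that no planned data can meet.

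**Working it through.** No figure in the article bears on this point, and the sample size of 370 is not in question. The check sets the stated schedule against the stated outcomes.

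**1. Is any of the 12 visits postnatal?** Follow-up visits are listed at 20, 24 and 28 weeks (3), at 30, 32, 34 and 36 weeks (4), and at 37, 38, 39 and 40 weeks (4). That gives 3 + 4 + 4 = 11. With the baseline visit, 11 + 1 = 12, which is exactly the stated total; the screening day is visit 0 and is counted apart. The antenatal schedule therefore uses up all 12 visits. The assessments listed for visits 2–12 are symptoms of pre-eclampsia, weight, blood pressure and urine, with nothing on the newborn or the puerperium. Home visits replace missed visits and add no later contact.

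**2. Which outcomes can fall after delivery, and what covers them?**

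| Outcome | During the birth admission | After discharge, or birth elsewhere |
|---|---|---|
| Early neonatal death | Hospital record | No stated contact |
| Intracranial bleeding (newborn) | Hospital record | No stated contact |
| Postpartum haemorrhage | Hospital record | No stated contact |
| HDU/ICU stay | Hospital record | No stated contact |
| Haematoma | Hospital record | No stated contact |
| Maternal death | Hospital record | No stated contact |

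That is 2 neonatal + 4 maternal = 6 outcomes. NICU admission is a seventh that follows birth, but it will mostly belong to the birth admission. The middle column relies on Source documents, which names hospital records. The right-hand column matters because the article nowhere says that all women will deliver at this hospital, and it foresees women who cannot travel to it.

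**3. Do the adverse-event rules fill the gap?** Safety recording ties collection to the clinical visits, which step 1 shows are all antenatal. Data collection and monitoring says more broadly that events are noted over the whole study period, but for an individual woman no end after birth is given. The two statements leave the postnatal window open.

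**4. Is there anything behind the long-term infant statement?** No infant outcome or contact after birth is defined. The calendar leaves little room either. Timelines with deliverables puts recruitment up to month 33 of 36.

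- A woman enrolled at 16 weeks reaches 40 weeks after 40 − 16 = 24 weeks, and one enrolled at 12 weeks after 40 − 12 = 28 weeks.
- At 4.345 weeks per month these are 24/4.345 = 5.5 and 28/4.345 = 6.4 months.
- If enrolment itself runs to month 33, the last women reach 40 weeks at about month 33 + 5.5 = 38.5 to 33 + 6.4 = 39.4, past the stated total.
- If month 33 is meant to include treatment, only the 3 months for analysis and reporting remain.

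Neither reading allows long-term infant data.

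**The case against.** The fairest reading against the point is that the rule has two halves. Follow-up runs to delivery, and the fetomaternal outcome is then noted; the outcome list defines what that covers and has its own postpartum block. Adverse events are to be recorded throughout the study, serious events are notified at once, and hospital records are source documents. Figures 1 and 2, which hold the schedules, are not shown. A condensed article also commonly leaves outcome windows to the full protocol.

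Much of this stands. A reader might infer that these outcomes cannot be ascertained at all. The article does not support that: most haemorrhage, haematoma, HDU/ICU stay and in-hospital death will appear in the birth record. What remains is the part after discharge or at another place of birth, which none of these provisions reaches. A postnatal visit in a missing figure would contradict the total of 12.

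A reader might also infer that women with no postnatal record would be counted as free of events. No section says so. The sections on case report forms, missing data and loss to follow-up point the other way: blanks must be explained, multiple imputation and sensitivity analyses are planned, and reasons for loss are recorded.

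It is tempting to size the loss from the postpartum haemorrhage rates in the Introduction (10.2% vs 7.8%). Those compare aspirin users with non-users, whereas both groups here take aspirin, so they do not give an expected difference between doses. Loss in one group must also not be set against a between-group difference: if both groups lose the same fraction f, the ratio (1 − f) × 10.2 / ((1 − f) × 7.8) stays at 10.2/7.8 = 1.31. The article gives no reason to expect unequal loss under blinding.

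Finally, the side-effect objective is limited to pregnancy, and all of these are secondary outcomes.

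**Conclusion.** The point holds as a cheap improvement, not as a flaw in the trial's main question. A stated follow-up rule, repeated in three sections, ends before six listed secondary outcomes have run their course, and none of the 12 visits is postnatal. Ascertainment of those outcomes therefore depends on how long mother and newborn stay and where the birth takes place. The number of events lost cannot be derived from the article, which gives neither length of stay nor the share of births elsewhere. Loss that is similar in both groups would lower the counts and precision without altering the ratio.

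The primary outcome, preterm pre-eclampsia before 37 weeks, is not affected. The long-term infant statement is unsupported by any outcome, contact or calendar time. The conclusion assumes that the missing figures agree with the text's count of 12 visits.

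**What to change.** - In Comparison, Study procedure and Treatment period, replace delivery as the end of follow-up with a fixed point after birth. One workable choice is 7 completed days after birth or discharge of mother and newborn, whichever is later; another window would serve if it is stated.
- In Safety recording and in Data collection and monitoring, apply the same window to adverse events.
- Name the sources: hospital records of mother and newborn, plus one phone call at the end of the window by the project staff who already make reminder calls and home visits. The call should ask about care or birth at other hospitals.
- Record women without this contact as missing for these outcomes, so that the existing missing-data provisions apply.
- Delete the sentence on long-term infant health from Need for the study.

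The cost is one call and one case report form page per participant, together with the wording changes. Dose, sample size and primary analysis stay as they are.
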